### Intervention

#### Control group

Families in the control group will receive usual care. Usual care includes the following: First, the issuance of health handbooks, which include breast cancer-related knowledge, postoperative rehabilitation exercise guidance, clinical nursing practice guidelines for preventive behavior of breast cancer-related lymphedema and a breast cancer postoperative follow-up checklist. Second, a WeChat group will be established where researchers answer questions and share disease-related knowledge with participants. Finally, Everyone will be encouraged to share positive experiences related to the disease in the WeChat group to encourage and support each other.

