**Methods:**

The trial will recruit 80 breast cancer families and randomly assign them to experimental and control groups in a 1:1 ratio. The control group will receive routine care, and the intervention group will receive a 6-week one-on-one online family resilience intervention based on the control group. Two groups of subjects will be assessed at baseline and at 1 week, 1 month, and 3 months after the intervention. The primary outcome is family resilience, and the secondary outcomes are coping style, social support, family disease burden, and levels of anxiety and depression.

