### Hypotheses

The research hypotheses are as follows:

After the intervention, the family resilience level of the intervention group will be significantly improved compared with that before the intervention.After the intervention, the family resilience level of the intervention group will be significantly improved compared with that of the control group.After the intervention, other aspects related to family resilience in the intervention group, such as the family disease burden and anxiety and depression levels of patients and their families, will be significantly relieved, and the level of disease coping and social support will be improved accordingly.

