### Sample size

Study sample size calculated by PASS15. Based on previous survey results (Lim and Han, 2013), family resilience measured by the Family Resilience Index (FHI) changed by 0.29 points before and after the intervention with a statistical power of 0.9, 2.5% significance, and using a one-tailed test to calculate a sample size of 36 families in each group (72 families in total; McCubbin et al., 1996). Assuming a 10% dropout rate in the intervention, each group would need to include 40 families (80 families in total). The sample size calculation formula is as follows:

$$n=\frac{{\left({Ζ}_{\alpha }+{Ζ}_{\beta }\right)}^{2*}2\sigma^{2}}{\delta^{2}}$$

A series of measures will be taken to reduce attrition during the intervention. First, during the intervention recruitment phase, the patient’s attending physician or other medical staff will be invited to answer the patient’s and family’s concerns to increase participants’ trust in the program. Second, a WeChat group will be established where researchers answer questions and share disease-related knowledge with participants. The third is to invite breast cancer treatment experts and nursing experts to control the quality of the entire intervention process, and timely answer questions from patients and their families about disease treatment and care. Fourth, during the intervention, participants can get in touch with the research team to get answers to any difficulties involved in the implementation and application of the intervention content. Finally, at the end of the program, the research team will present the participants with a nice gift to express their gratitude.

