#### Experimental group

The experimental group will implement one-on-one online family resilience intervention on the basis of usual care. Intervention implementation will be led by a professionally trained nursing graduate student and a breast cancer-related unit nurse. A breast cancer therapist and a psychobehavioral specialist will guide and supervise the implementation of the intervention. The entire intervention process includes a preintervention program introduction, six family meetings, and a postintervention summary. The frequency of interventions is weekly, with each meeting lasting 25–30 min. The first meeting, combined with patient follow-up time, will be an face-to-face family meeting with participating families, and the next five meetings will be online family meetings. The first follow-up visit to the hospital after surgery is usually approximately 1 week after surgery. A quiet, undisturbed environment will be chosen for family meetings. The specific time for each family meeting must be agreed upon in advance with participating families.

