Content	A brief recap of last week’s meeting. Let the primary caregiver to review issues encountered during the patient’s care over the past week. Combined with pictures and texts, it provides nursing methods and precautions for different treatments for breast cancer patients and their families. Have patients and primary caregivers share their emotions and stress over the past week. Help patients and primary caregivers learn ways to manage stress and emotions to stay positive and optimistic by combining pictures, text and videos.
Homework	Review the content of this meeting through electronic meeting materials. Patients and primary caregivers are encouraged to discuss their own stressors and ways to relieve stress with researchers (*via* voice or text message or phone call).
Family Organization - Family treasure (Third week after surgery)	
Theme	Discover Available Resources
Form	Online family meeting
Target	Identify the family’s own strengths and available resources and learn how to use them. Summarize the experience of overcoming difficulties from past experiences.
Content	A brief recap of last week’s meeting. Combine pictures and words to show participants’ families what family resources, social resources and family strengths are. Help family members discover and demonstrate their family strengths and resources. Discuss success and failure cases and their characteristics in overcoming difficulties through family conversations, and summarize experiences. Discuss together how to leverage existing family strengths and resources to address current issues and challenges. Encourage different families to exchange experiences through WeChat groups and provide emotional support to each other.
Homework	Review the content of this meeting through electronic meeting materials. Give researchers examples of how their resources will be used in the future (*via* voice or text message or phone call).
Family Organization - Intimacy has a way (Fourth week after surgery)	
Theme	Improve Family Cohesion
Form	Online family meeting
Target	Create simple and effective family rules to promote family relationships and strengthen family bonds.

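### The comparator is labelled routine or usual care but includes study-run WeChat support, so the trial estimates an increment over enhanced usual care; separately, the power statement takes a before-after change as the between-arm difference

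*Protocol article*

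**What the plan says.** **The label.** The abstract of the protocol article (Methods) states: "The control group will receive routine care". Study design uses the term usual care, and the Control group section repeats it: "Families in the control group will receive usual care".

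**The content.** The Control group section lists three parts: health handbooks, a WeChat group, and mutual support within that group. On the second part it says: "Second, a WeChat group will be established where researchers answer questions and share disease-related knowledge with participants". On the third: "Everyone will be encouraged to share positive experiences related to the disease in the WeChat group to encourage and support each other".

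**The same group elsewhere.** The Sample size section contains the WeChat sentence again, word for word, as the second item of a list that opens: "A series of measures will be taken to reduce attrition during the intervention". In Table 1, the third-week programme content includes: "Encourage different families to exchange experiences through WeChat groups and provide emotional support to each other".

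**The contrast.** The Experimental group section states: "The experimental group will implement one-on-one online family resilience intervention on the basis of usual care". Hypothesis 2 is that "the family resilience level of the intervention group will be significantly improved compared with that of the control group". Hypothesis 3 predicts improvement in the secondary outcomes, social support among them, and names no comparator.

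**The sizing.** The Sample size section takes a change of 0.29 points from before to after the intervention, on the family resilience index of an earlier study. It puts this into a two-group formula with power 0.9 and one-tailed 2.5% significance. The result is 36 families per group, or 40 after 10% dropout.

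**The concern.** A group that the trial sets up, that researchers staff and that is listed as a retention device is a study procedure. Nothing in the document presents it as something the hospitals already provide. Its peer-support element also recurs inside the programme. The name in the abstract therefore does not match what controls receive.

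At stake is the meaning of the estimate. Reported as an effect against routine care, a positive result would describe a comparison that was not made. A null result would show only that no increment over a supportive package was detected. That matters most for social support, the listed outcome closest to what the WeChat group offers. Abstract readers see only the words routine care.

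The sizing raises a second, separate question. A before-after change in treated families is not in general the difference between two randomised arms. The question would arise with any comparator, but it has more force when controls also get researcher contact and peer support.

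**Working it through.** **1. Which parts are shown to be study-added**

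| Control component | Evidence in the article | Shown to be study-added? |
|---|---|---|
| Health handbooks | Control group section only | No; may be existing care |
| WeChat group with researcher answers | To be established; repeated under Sample size as an attrition measure | Yes |
| Encouraged sharing and mutual support | Takes place inside that group; similar activity in Table 1, week 3 | Yes, since it depends on the group |

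**2. What the randomised contrast estimates**

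Let P be the change common to both arms (package, recovery, time) and M the further change due to the programme. The intervention arm changes by P + M and the control arm by P, so the difference is M. This is the programme's increment over the package. If the two overlap in effect, M is smaller than the programme would achieve alone. An effect against care without the WeChat support cannot be recovered, because no arm goes without it.

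**3. The plan's own figure**

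Inputs from Sample size: δ = 0.29, one-sided α = 0.025, power 0.90, n = 36 per group. No SD is given, so 36 cannot be reproduced independently and the SD is back-solved.

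- Formula: n = (z_α + z_β)² × 2σ² / δ², with z_α + z_β = 1.960 + 1.282 = 3.242 (square about 10.51).
- Upper limit, n = 36: σ = 0.29 × √(36/2) / 3.242 = 0.380.
- Lower limit, just above n = 35: σ = 0.29 × √(35/2) / 3.242 = 0.374.
- Dropout: 36 / 0.9 = 40 per group, as stated.

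**4. Two readings of 0.29**

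- If 0.29 is M, the between-arm difference, power is 90% whatever the size of P, because P cancels.
- If 0.29 is P + M, the total before-after change, the between-arm difference is 0.29 − P. The text describes the figure in this second way, and using it as δ then sets P to zero.

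**5. Size under the second reading**

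Assume σ = 0.379, 36 analysed per group, and a share f of the 0.29 that also occurs in controls. The document gives no value for f.

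Power = Φ( 0.29(1 − f) / (σ√(2/36)) − 1.960 ), where σ√(2/36) = 0.379 × 0.2357 = 0.0893.

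| f (assumed) | Between-arm difference | Power | n per group for 90% power, before / after 10% dropout |
|---|---|---|---|
| 0 | 0.290 | 90% | 36 / 40 |
| 10% | 0.261 | 83% | 45 / 50 |
| 20% | 0.232 | 74% | 57 / 64 |
| 30% | 0.203 | 62% | 74 / 83 |

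**The case against.** **The design is open and the comparison valid.** The Control group section itemises the package, the experimental arm receives it too, and hypothesis 2 is worded against the control group rather than against routine care. This stands. A reader might infer that the trial cannot answer its stated question, or that controls are contaminated in a way that biases the comparison. The document supports neither: the add-on contrast is sound and hypothesis 2 can be tested. The fault is in the name and in the claim that follows from it.

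**Control improvement need not cost power.** This also stands. A reader might infer that 90% power requires the control arm not to change at all. It does not: gains common to both arms cancel, and a between-arm difference of 0.29 keeps the power whatever both arms gain. What remains is that the protocol justifies 0.29 as a before-after change and does not say that it is net of change in a comparison group.

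**The magnitudes are assumed.** True. The SD is back-solved and f is a chosen range. The 0.29 is on the earlier study's index, whereas this trial's primary outcome is the Chinese Family Resilience Assessment. The figures show sensitivity and do not forecast this trial's power.

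**The overlap with the programme is small.** WeChat exchange is one sentence in week 3 of a programme built on one-on-one meetings, and no passage says the control group's WeChat is aimed at social support. This is fair and limits how much dilution one should expect. It does not restore the routine care label.

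**A misread null result is speculation.** It is a risk rather than something the text fixes, since a reader of the full article can see the comparator. It applies mainly to readers of the abstract.

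**Conclusion.** The point holds as one of naming, interpretation and stated power basis. The control condition is enhanced usual care, and the trial estimates the increment of the six family meetings over it. It does not estimate an effect against routine care. Internal validity is not in question. Calling the whole package study-built would go too far, because only the WeChat elements are shown to be added by the study.

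On power, the stated 90% requires a between-arm difference of 0.29. The protocol supports that number only with a before-after change, so it relies on none of that change also occurring in controls. If 10% to 30% of it does, power is about 83% to 62%. This rests on a back-solved SD of about 0.37 to 0.38, 36 analysed families per group, and shares that are assumptions and cannot be derived from the document.

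**What to change.** 1. In the abstract, Study design and Control group sections, name the comparator enhanced usual care (handbook plus study-run WeChat support). Word hypotheses 2 and 3 and the conclusion as the increment of the programme over that package.

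2. In Sample size, state that 90% power requires a between-arm difference of 0.29. State the SD used, and show the power if part of the 0.29 also occurs in controls. With the back-solved SD, and marked as assumed illustrations, this is 83% at 10%, 74% at 20% and 62% at 30%.

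The content of the control arm need not change; removing the peer encouragement would be a design preference. The cost is wording only, with no extra families or procedures. The downside is a narrower claim and a less favourable power statement.

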### Limitations

This study may have some limitations. First, there are many family meetings in the intervention program, and subjects may not be able to attend all of them due to physical or other reasons, which will lead to sample loss that may have an impact on the study results. Second, because of the nature of the study, it was not possible to blind the interventionists. Therefore, this study will arrange for independent researchers to collect and evaluate the data. Finally, while each family meeting will be held in an isolated quiet setting, some subjects may be contaminated due to subject recruitment and the first family meeting being held in the same department of the hospital. Therefore, when arranging meetings for families in the intervention group, researchers should try to choose an appropriate place and time to avoid crowd gathering and contamination between study subjects.

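### WeChat exchange is part of usual care in both arms and is used again in the week-3 intervention session, and nothing keeps the arms apart, so the plan as written permits contamination that its safeguard does not cover

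*Protocol article*

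**What the plan says.** Four parts of the protocol article bear on this point.

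- **Control group.** Usual care has a WeChat component: "Second, a WeChat group will be established where researchers answer questions and share disease-related knowledge with participants". The section then adds: "Everyone will be encouraged to share positive experiences related to the disease in the WeChat group to encourage and support each other".
- **Experimental group.** Usual care is the base for this arm too: "The experimental group will implement one-on-one online family resilience intervention on the basis of usual care". In Table 1, the session for the third week after surgery, on discovering available resources, includes: "Encourage different families to exchange experiences through WeChat groups and provide emotional support to each other".
- **Sample size.** Among the measures against attrition, the control-arm sentence reappears almost word for word: "a WeChat group will be established where researchers answer questions and share disease-related knowledge with participants". It is in the singular and makes no distinction by arm.
- **Limitations.** Contamination is acknowledged by one route: "some subjects may be contaminated due to subject recruitment and the first family meeting being held in the same department of the hospital". The response is that "researchers should try to choose an appropriate place and time to avoid crowd gathering and contamination between study subjects".

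The sample size calculation makes no allowance for contamination.

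**The concern.** The trial tests a psychosocial programme against usual care on a self-reported family outcome. That comparison depends on control families not receiving the programme, or a share of its benefit, from families who do. The meetings are held with one family at a time, so WeChat is the only contact between families that the programme itself describes. It is also a component of what control families receive.

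If the two meet in the same chat, control families can pick up intervention families' accounts of their strengths, resources and ways of coping, along with their emotional support. That would raise control scores and shrink the measured difference in family resilience. Social support and coping style, both secondary outcomes, are close to what peer exchange acts on and could be affected in the same way. Once exposure has happened in a shared chat, no analysis can remove it.

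**Working it through.** **Step 1. Follow the channel through the article.**

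| Question | What the article gives |
|---|---|
| Do control families have a WeChat group? | Yes, as part of usual care (Control group) |
| Do intervention families have it too? | Yes, because they receive usual care (Experimental group) |
| Is WeChat also used by the programme? | Yes, in the week-3 session (Table 1) |
| Is membership defined by arm? | No. Sample size and Control group use the singular; Table 1 uses the plural |
| Does the contamination safeguard cover it? | No. It covers the place and time of meetings (Limitations) |

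The Experimental group section makes only the first of the six meetings face-to-face and the other five online. A safeguard about place and time in the hospital therefore does little after the first week, while the chat can run throughout.

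**Step 2. Look at the plan's own sample size.** Inputs from the Sample size section: 36 families per group before dropout, power 0.90, one-sided alpha 0.025, difference 0.29 points. The printed formula is

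n = (z_α + z_β)² · 2σ² / δ²

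No standard deviation is stated, so the 36 cannot be reproduced independently. Solving backwards:

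- z_α + z_β = 1.960 + 1.2816 = 3.2415
- δ/σ = 3.2415 × √(2/36) = 0.764
- implied σ = 0.29 / 0.764 ≈ 0.38

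The dropout step does reproduce: 36 / 0.90 = 40 per group.

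**Step 3. Illustrate dilution.** Let f be the fraction of the effect lost because control families gain some of it. The documents give no value for f, so the values below are assumptions. With 36 evaluable families per group,

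power = Φ(3.2415 × (1 − f) − 1.960)

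| f (assumed) | Standardised effect | Power at 36 per group | n per group for 90% power | n per group after 10% dropout |
|---|---|---|---|---|
| 0 | 0.76 | 90% | 36 | 40 |
| 10% | 0.69 | Φ(0.957) = 83% | 45 | 50 |
| 25% | 0.57 | Φ(0.471) = 68% | 64 | 72 |

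The fourth column is 36 / (1 − f)², rounded up: 36 / 0.81 = 44.4 and 36 / 0.5625 = 64. The last column divides by 0.90 and rounds up.

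**The case against.** The strongest reply is that a shared chat is inferred. Neither WeChat sentence says who belongs to the group. One of them stands under the Control group heading, where it can be read as referring to control families alone, and Table 1 uses the plural. Giving both arms usual care means both have a WeChat component, which is not the same as being in one chat. Membership rules could also be left to a fuller protocol or intervention manual.

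The first part of this stands. A reader might infer that all families are in one group; the documents allow that reading but do not state it. The second part carries less weight. The article takes up contamination itself and fixes a safeguard, and that safeguard misses a channel which the article elsewhere builds into both arms.

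Three further limits also stand.

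- A reader might infer that intervention families are told to post what they have learned. Table 1 only encourages an exchange of experiences and support, in one session of six. Meeting materials go to the intervention group, and homework goes to the researchers.
- Peer sharing among control families is declared usual care. Within their own group it is the comparator as designed and is not leakage.
- A reader might take a severe loss of power from the formula: an assumed 50% dilution would give about 37%. Nothing in the documents suggests that chat posts would deliver half the effect of six guided meetings.

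A mixed chat could also show control families what the other arm receives, although the article describes participants as blinded. Whether participants can be blinded at all in this design is a separate question that does not depend on WeChat.

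**Conclusion.** The concern holds as a gap in the design's protection against contamination. The plan puts a WeChat group into the care of both arms, uses WeChat again for exchange between families in week 3, does not separate the arms, and offers a safeguard that does not reach this route. A team following the text could run one mixed chat without departing from the plan. Any resulting leakage of benefit would bias the primary between-group comparison toward zero.

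The size is not known. The figures of about 83% and 68% power rest on assumed dilutions of 10% and 25%, and on a standardised effect of 0.76 that is back-solved because the article states no standard deviation. They show how sensitive the design is and are not forecasts. The documents do not establish that the arms share a chat or that contamination will occur. The point should be settled before enrolment; the change is simple and the harm cannot be repaired afterwards.

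**What to change.** 1. In the Sample size, Control group and Experimental group sections and in the week-3 row of Table 1, state that one closed WeChat group is run per arm.
2. State that the week-3 exchange between families takes place only in the intervention-arm group.
3. State that no materials, homework or themes from the coping-focused family resilience programme (CFFRI) are posted in the usual-care group.
4. In Limitations, add WeChat contact to the contamination paragraph and cite the separate groups as the safeguard.

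The cost is two chats to moderate instead of one. If separate groups are already intended, the change is one of wording only. The sample size need not change on this ground, because the dilution figures are illustrative and separate groups address the route directly.
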